## LIST OF ABBREVIATIONS AND RELEVANT DEFINITIONS

|                  |                                                                                                                                                                                                                                                                                                                                           |
|------------------|-------------------------------------------------------------------------------------------------------------------------------------------------------------------------------------------------------------------------------------------------------------------------------------------------------------------------------------------|
| AE        | Adverse Event                                                                                                                                                                                                                                                                                                                             |
| AR        | Adverse Reaction                                                                                                                                                                                                                                                                                                                          |
| BIA       | Bio-electrical impedance analysis                                                                                                                                                                                                                                                                                                         |
| CCMO      | Central Committee on Research Involving Human Subjects; in Dutch: Centrale Commissie Mensgebonden Onderzoek                                                                                                                                                                                                                               |
| CEA       | Cost-Effectiveness Analysis                                                                                                                                                                                                                                                                                                               |
| CUA       | Cost-Utility Analysis                                                                                                                                                                                                                                                                                                                     |
| CSMA      | Cross-sectional Skeletal Muscle Area                                                                                                                                                                                                                                                                                                      |
| CTCAE     | Common Terminology Criteria for Adverse Events                                                                                                                                                                                                                                                                                            |
| DSMB      | Data Safety Monitoring Board                                                                                                                                                                                                                                                                                                              |
| ESPEN     | European Society for Clinical Nutrition and Metabolism                                                                                                                                                                                                                                                                                    |
| EU        | European Union                                                                                                                                                                                                                                                                                                                            |
| EWGSOP2   | European Working Group on Sarcopenia in Older People 2                                                                                                                                                                                                                                                                                    |
| GDPR      | General Data Protection Regulation; in Dutch: Algemene Verordening Gegevensbescherming (AVG)                                                                                                                                                                                                                                              |
| GLIM      | Global Leadership Initiative on Malnutrition                                                                                                                                                                                                                                                                                              |
| HU        | Hounsfield Unit                                                                                                                                                                                                                                                                                                                           |
| LSMI      | Lumbar Skeletal Muscle Index                                                                                                                                                                                                                                                                                                              |
| METC      | Medical research ethics committee (MREC); in Dutch: medisch-ethische toetsingscommissie (METC)                                                                                                                                                                                                                                            |
| MUST      | Malnutrition Universal Screening Tool                                                                                                                                                                                                                                                                                                     |
| PG-SGA SF | Patient Generated Subjective Global Assessment Short Form                                                                                                                                                                                                                                                                                 |
| REE       | Resting Energy Expenditure                                                                                                                                                                                                                                                                                                                |
| (S)AE     | (Serious) Adverse Event                                                                                                                                                                                                                                                                                                                   |
| Sponsor   | The sponsor is the party that commissions the organisation or performance of the research, for example a pharmaceutical company, academic hospital, scientific organisation or investigator. A party that provides funding for a study but does not commission it is not regarded as the sponsor, but referred to as a subsidising party. |
| SUSAR     | Suspected Unexpected Serious Adverse Reaction                                                                                                                                                                                                                                                                                             |
| TUG       | Timed Up and Go Test                                                                                                                                                                                                                                                                                                                      |
| UMCG      | University Medical Center Groningen                                                                                                                                                                                                                                                                                                       |
| WHO       | World Health Organization                                                                                                                                                                                                                                                                                                                 |

**WMO**

Medical Research Involving Human Subjects Act; in Dutch: Wet Medisch-wetenschappelijk Onderzoek met Mensen

## SUMMARY

**Rationale:** up to 60% of patients with head and neck cancer are malnourished upon first presentation. Malnutrition has been associated with more adverse events and lower quality of life and survival. According to current Dutch guidelines, patient with high risk of malnutrition receive pretreatment dietary treatment. A recent study has shown that patients with low to medium risk of malnutrition, may benefit from additional screening and subsequent nutritional prehabilitation.

**Objective:** to investigate the effect of nutritional prehabilitation on adverse events in patients with locoregionally advanced head and neck cancer and with low to medium risk of malnutrition. To evaluate its effect on patient-reported quality of life outcome measures, recurrence and (disease-specific and overall) survival. To evaluate the cost-effectiveness of nutritional prehabilitation compared to standard care.

**Study design:** a single-center, non-blinded, randomized controlled trial.

**Study population:** patients with stage III and stage IV primary mucosal squamous cell carcinoma located in the oral cavity, oropharynx, hypopharynx or larynx treated with curative intent and with low or medium risk of malnutrition.

**Intervention:** one group will receive nutritional prehabilitation and one group will receive standard care (which means they will not receive nutritional prehabilitation).

**Main study parameters/endpoints:** adverse events (i.e., intra- and postoperative complications and (chemo)radiotherapy toxicity). Complications will be measured within 30 days after surgery using the Clavien-Dindo classification. Toxicity will be evaluated using the Common Terminology Criteria for Adverse Events, version 4.0, 6 weeks after the start of (chemo)radiotherapy.

### **Nature and extent of the burden and risks associated with participation, benefit and group relatedness:**

Patients will be asked to undergo several measurements that are not part of our current standard practice. These measurements entail one grip strength measurement, three BIA-measurements and the following questionnaires: EAT-10, iMCQ and iPCQ at respectively six time points, four time points and four time points. Furthermore, the intervention itself will require three sessions with a dietitian, either during a regular visit at the outpatient department or through a telephone/video call. The time burden of these extra measurements and the intervention is 185 minutes on average.

There are negligible risks associated with the investigational treatment.

We expect that nutritional prehabilitation will lead to fewer (serious) complications and side effects compared to no nutritional prehabilitation. We expect a higher quality of life, equal chance of recurrence and better survival.

## 1. INTRODUCTION AND RATIONALE

Head and neck cancers are among the most frequent tumors in the world with an estimated 835.000 new cases and 428.000 deaths in 2018 globally [1]. Patients with head and neck cancer are eminently at risk for malnutrition due to the location of the tumor in the upper aero-gastrointestinal tract. Up to 60% of patients with head and neck cancer are malnourished upon first presentation [2-5]. Malnutrition has been associated with lower quality of life and treatment tolerance, and more postoperative complications, toxicity and mortality [6-8]. To identify patients in need of nutritional intervention, malnutrition risk is screened using the Malnutrition Universal Screening Tool (MUST) at the University Medical Center Groningen (UMCG). According to current Dutch guidelines, dietary therapy, including counseling by a dietitian, is started in patients with high risk of malnutrition, whereas patients with low to medium risk of malnutrition do not routinely receive dietary therapy [9]. A recent study in patients with head and neck cancer has shown that postoperative complications occur more frequently in patients with medium risk of malnutrition, but not in patients with high risk of malnutrition [10]. This is very likely to be explained by the effectiveness of dietary interventions in patients with high risk of malnutrition. Patients with low to medium risk of malnutrition, may benefit from additional screening and subsequent nutritional prehabilitation.

In patients with hepatobiliary, colorectal and upper gastrointestinal cancer treated with surgery, a recent meta-analysis found that duration of hospital stay was significantly shorter in patients participating in a prehabilitation program [11]. While no significant difference in complication rate or survival rate was found, other studies have noted a trend towards less complications [12]. Such intervention studies have not been performed in patients with head and neck cancer yet. **Efforts to better identify and treat patients with a need for nutritional prehabilitation thus minimizing treatment-related adverse events (i.e., intra- and postoperative complications, toxicity and mortality) and maximizing quality of life, represent an unmet need for patients with head and neck cancer.**

## **2. OBJECTIVES**

Primary Objective: to investigate the effect of nutritional prehabilitation on adverse events (complication rates and (chemo)radiotherapy toxicity) in patients with locoregionally advanced head and neck cancer and with low to medium risk of malnutrition.

Secondary Objective(s):

To investigate the effect of nutritional prehabilitation on patient-reported quality of life outcome measures, recurrence and (disease-specific and overall) survival in patients with locally advanced head and neck cancer and with a low to medium risk of malnutrition;

To evaluate the cost-effectiveness of nutritional prehabilitation compared to standard care.

### 3. STUDY DESIGN

A single-center, non-blinded, randomized controlled trial will be performed. The study will be performed within the Department of Otorhinolaryngology – Head and Neck Surgery, Department of Oral and Maxillofacial Surgery and the Department of Radiotherapy at the University Medical Center Groningen.

Figure 1 visualizes the inclusion of patients. All head and neck cancer patients are screened using the MUST at baseline. Patients with high risk of malnutrition are treated by a dietitian as part of our current standard practice. Patients with low to medium risk of malnutrition are eligible for inclusion. As soon as they are enrolled, they will be randomized.

[figure not shown]

**Figure 1.** Study flow.

*MUST = Malnutrition Universal Screening Tool.*

#### *Intervention*

Included patients will be randomly assigned to one of two groups: nutritional prehabilitation or standard care. The nutritional prehabilitation intervention is not different from the treatment we offer patients with high risk of malnutrition based on the MUST in daily clinical practice. Nutritional prehabilitation will typically take around three to four-and-a-half weeks, given a pre-treatment time window in patients with head and neck cancer of four to five weeks from first referral to the outpatient clinic to the start of treatment. Further information on the intervention can be found under subheading 5.1 (treatment). Patients receiving standard care will not receive any nutritional counseling or nutritional intervention before treatment commences. Patients will be monitored for two years. Measurement moments will coincide

with regular follow-up visits to the outpatient departments. Further information on the outcomes to be measured can be found under subheading 8.1 (study parameters/endpoints).

## **4. STUDY POPULATION**

### **4.1 Population (base)**

Subjects will be drawn from our population of head and neck cancer patients, using the inclusion and exclusion criteria mentioned below. It is very likely we will be able to recruit the planned number of patients from the defined source population. We see on average 111 patients per year that are eligible for inclusion. Assuming a participation rate of 80%, we will be able to include the necessary 128 patients in approximately 17 months' time.

### **4.2 Inclusion criteria**

In order to be eligible to participate in this study, a subject must meet all of the following criteria:

- Primary mucosal squamous cell carcinoma;
- Located in the oral cavity, oropharynx, hypopharynx or larynx;
- Locoregionally advanced disease defined as stage III and stage IV disease. For oropharynx malignancies the HPV-negative TNM-staging is used at the time of inclusion;
- Treated with curative intent;
- Low or medium risk of malnutrition based on the MUST;
- Pre-treatment CT scan performed up to 30 days before treatment;
- Age  $\geq 18$  years;
- Written informed consent.

### **4.3 Exclusion criteria**

A potential subject who meets any of the following criteria will be excluded from participation in this study:

- Previous surgical or radiotherapeutic treatment of the neck;
- Multiple simultaneous primary malignancies;
- Disability that could interfere with questionnaire fulfillment.

### **4.4 Sample size calculation**

We performed a power analysis to calculate the sample size needed. Intervention studies evaluating the effect of nutritional prehabilitation in patients with head and neck cancer have not been performed previously. Therefore, the numbers used for the power analysis are based on studies on the association between malnutrition/radiological sarcopenia and adverse events in patients with head and neck cancer. We expect the rate of adverse events in the intervention arm to be 15% based on the rates of adverse events in well-nourished/non-sarcopenic study populations [8, 13]. We expect the rate of adverse events

in the control arm to be 40% based on reported rates of adverse events in malnourished patients [8] and reported odds ratios in studies on the association between sarcopenia and adverse events [13, 14]. To detect a clinically relevant difference of 25% between the intervention and control arm, with a two-sided alpha of 0.05 and a power of 80%, a minimum of 61 patients per arm are needed. With an expected drop-out of 5%, we will include a total of 128 patients. This analysis was performed using G\*Power version 3.1.

## 5. TREATMENT OF SUBJECTS

### 5.1 Treatment

Included patients will be randomly assigned to one of two groups: nutritional prehabilitation or standard care. The nutritional prehabilitation intervention is not different from the treatment we offer patients with high risk of malnutrition based on the MUST in daily clinical practice.

Nutritional prehabilitation includes nutrition counseling and education by a dietitian, oral nutritional supplements, and enteral and/or parenteral nutrition support, as appropriate for each individual patient and in accordance with the guidelines proposed by the World Health Organization (WHO), ESPEN and the National Institute for Health and Care Excellence [15-17]. An adequate intake will be supported that is based on the balance between the patient's total energy and protein needs, disease status, current intake, lifestyle and food preferences.

An energy and protein enriched diet will be advised. We aim for an energy intake of the resting energy expenditure (REE) plus 30 to 50% for physical activity level, illness and thermic effect of food. The equation of the Food and Agriculture Organization, WHO and United Nations University will be used to calculate the REE [15]. We aim for a protein intake of 1.2 to 1.5 g/kg/day in patients with a BMI of 20-25 kg/m^2. For a BMI of less than 20 kg/m^2, the protein requirement will be corrected to a BMI of 20 kg/m^2 [18]. For a BMI of more than 25.0 kg/m^2, Gallagher's formula will be used to calculate protein requirement, according to local guidelines [19]. Vitamins, minerals and trace elements will be supplied in amounts equal to the recommended daily allowance and we will not be using high-dose micronutrients in the absence of specific deficiencies [16].

Patients who are able to use oral intake, will receive dietary advice by a dietitian and will be offered oral nutritional supplements to meet estimated nutritional requirements. If oral intake is not possible or insufficient despite nutritional interventions (i.e., counselling and oral nutritional supplements), we will discuss enteral nutritional support with the patient. Insufficient intake is defined as less than 50% of the requirement for more than one week or only 50-75% of the requirement for more than two weeks, and these are thus the indications for enteral nutritional support [16]. If enteral nutritional support is not sufficient or not feasible, we will advise parenteral nutrition support.

If oral food intake has been decreased severely for a prolonged period; oral, enteral or parenteral nutrition will be increased slowly over several days and additional precautions

will be taken to prevent a refeeding syndrome. Patients who meet the following criteria are at high risk of developing refeeding problems according to the NICE guideline on nutrition support for adults [17]:

- One or more of the following criteria:
  - o BMI  $<16 \text{ kg/m}^2$ ;
  - o Unintentional weight loss  $>15\%$  within the last three to six months;
  - o Little or no nutritional intake for more than 10 days;
  - o Low levels of potassium, phosphate or magnesium before feeding.
- Two or more of the following criteria:
  - o BMI  $<18.5 \text{ kg/m}^2$ ;
  - o Unintentional weight loss  $>10\%$  within the last three to six months;
  - o Little or no nutritional intake for more than five days;
  - o A history of alcohol abuse or drugs including insulin, chemotherapy, antacids or diuretics.

In these patients, nutrition support will be started at a maximum of 10 kcal/kg/day, increasing levels with 5 kcal/kg/day to meet or exceed full needs by four to seven days [17]. Vitamin B1 will be supplied in daily doses of at least 100 mg for at least five days as well as a balanced multivitamin and trace element supplement once daily for at least five days [20]. Potassium, phosphate and magnesium will be monitored and substituted, if necessary, by oral, enteral or parenteral route [17].

Dietetic consultations will be scheduled biweekly. Depending on the patients' needs and preferences, the frequency of consultations may be increased, e.g., in case of weight loss or inability to use oral intake. These consultations may take place in-person at the outpatient department or through video or telephone calls. The first consultation takes on average 30 minutes, follow-up consultations on average 15 minutes. We expect that in 10-20% of included patients dietary advice in the form of an energy and protein enriched diet will be sufficient and 80-90% of patients will be offered oral nutritional supplements to meet estimated nutritional requirements. Patients rarely need enteral nutritional support in this prehabilitation stage.

Nutritional prehabilitation will start as soon as patients are included in the study, which is within one week after their first visit to the outpatient department, depending on the time needed to consider participation in the trial. The expected variation in duration of the intervention is three to four-and-a-half weeks. The **prehabilitation** intervention ends as

soon as treatment for their head and neck cancer commences. Patients will still be receiving nutritional care as is standard care (i.e., postoperatively and/or during (chemo)radiotherapy). Nutritional care given during treatment is the same as nutritional care that is outlined in this paragraph (i.e., given as a prehabilitation intervention). Patients undergoing (chemo)radiotherapy are all counseled by a dietitian during their treatment. Patients undergoing surgery will receive nutritional care as indicated by their MUST score or as indicated by the “Perioperatief voedingsbeleid” guideline: inability to start oral intake within 48 hours after surgery or no more than 50% of the recommended daily energy intake on the fifth day postoperatively [21].

Patients enrolled in the control arm of the study will receive standard care, which means they will not receive any nutritional counseling or nutritional intervention before treatment commences.

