## **6. INVESTIGATIONAL PRODUCT**

Not applicable. The treatment (i.e., nutritional prehabilitation as described in paragraph 5.1) used in this study is part of standard clinical care, applied to patients with head and neck cancer with high risk of malnutrition based on the MUST. The execution of nutritional prehabilitation is in accordance with our current standard clinical practice, in line with local, national and worldwide guidelines.

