#### 8.1.3 Other study parameters

Baseline characteristics include age, gender, smoking status, alcohol use, tumor site, tumor stage, (intended) type of treatment, length, weight (loss), skeletal muscle mass, number of dietetic consultations, dietary intake using 24-hour recall, nutritional status

using the MUST, Global Leadership Initiative on Malnutrition (GLIM)-criteria, Patient Generated Subjective Global Assessment Short Form (PG-SGA SF) score and bio-electrical impedance analyses (BIA)-measurements, physical status using grip strength and Timed Up and Go Test (TUG), and skeletal muscle mass. Dietary intake using 24-hour recall, GLIM-criteria, PG-SGA SF and BIA-measurements will not only be performed at baseline to assess nutritional status, but also at the end of the dietetic intervention (or, for the control group, just before the treatment starts), and three months after the final treatment.

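### The control arm is barred from any nutritional care before treatment, with no written exception for a control recognised as high MUST risk during the wait

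*Protocol*

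**What the plan says.** The control condition is worded in two ways in the protocol.

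- Section 5.1 (Treatment) assigns controls to "standard care, which means they will not receive any nutritional counseling or nutritional intervention before treatment commences". Section 3, under Intervention, says the same: "Patients receiving standard care will not receive any nutritional counseling or nutritional intervention before treatment commences". Neither sentence has a qualifier.
- The Summary is narrower. The comparison group receives "standard care (which means they will not receive nutritional prehabilitation", and nothing further is withheld.

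The centre's usual practice depends on risk. Section 3 states: "Patients with high risk of malnutrition are treated by a dietitian as part of our current standard practice". Section 6 describes the trial intervention as "part of standard clinical care, applied to patients with head and neck cancer with high risk of malnutrition based on the MUST". Section 1 gives the same account of the Dutch guideline, and section 11.4.1 says that all high-risk patients receive dietary measures.

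Eligible patients have low or medium MUST risk at baseline (section 4.2). Section 8.1.3 repeats the 24-hour recall, GLIM criteria, PG-SGA SF and BIA "at the end of the dietetic intervention (or, for the control group, just before the treatment starts" and again three months after the final treatment. The MUST is not among the repeated measures.

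**The concern.** A control who enters at low or medium risk can deteriorate while waiting for treatment. The tumours are stage III or IV and lie in the upper aerodigestive tract, and section 1 stresses that their location puts patients at nutritional risk. If a clinician or the trial's own reassessment shows that such a patient has become high risk, the centre would normally involve a dietitian. The text of sections 3 and 5.1 does not allow this until treatment starts.

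Two things are at stake. The first is safety: a trial participant could be refused care that the same department gives its other high-risk patients. The second is fidelity of the comparator: the cost-effectiveness objective (section 2) and the economic evaluation (section 10.2) compare prehabilitation with standard care, and for these patients the control condition as written is less than standard care. The two wordings could also lead one clinician to follow the letter and another to refer.

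**Working it through.** **Step 1. Is an exception written anywhere?** These are the places where one could stand.

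| Protocol section | What it provides | Dietetic exception before treatment? |
|---|---|---|
| 5.2 and 5.3 | Both marked not applicable (5.3 concerns escape medication) | No |
| 5.1, care by MUST score | "Patients undergoing surgery will receive nutritional care as indicated by their MUST score", within the text on care after surgery or during (chemo)radiotherapy | No, it applies later |
| 8.4 and 8.4.1 | The subject may leave; the investigator may withdraw a subject for urgent medical reasons; no specific criteria | No |
| 8.6 | Standard medical treatment continues after withdrawal | Only outside the trial intervention, and dietetic care is not named |
| 9.4 | Tests or procedures as indicated, or referral to a general physician or medical specialist, in adverse-event follow-up | Dietetic care is not named |

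No exception is written.

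**Step 2. How could high risk be recognised?** Section 3 places the MUST at baseline, and no repeat before treatment is scheduled. Two routes remain: clinical contact during the wait, and the reassessment just before treatment. The second comes late, and dietetic care then follows soon, because all (chemo)radiotherapy patients are counselled during treatment and surgical patients are covered by MUST score or the perioperative guideline. A control whose decline nobody notices is treated as in usual care. The point therefore covers only recognised cases.

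**Step 3. What would the exception cost in power?** The documents give no share of affected controls, so this is an illustration.

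Inputs from section 4.4: control rate 40%, intervention rate 15%, two-sided alpha 0.05, 61 per arm. The plan's 61 is not reproduced by the usual methods: 49 per arm (pooled), 57 (continuity-corrected), 56 (Fisher exact). It errs on the large side and is a separate matter.

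Pooled test: power = Φ[(p1 − p2 − 1.96·se0)/se1], with se0 = √[2·p̄(1 − p̄)/61] and se1 = √[(p1(1 − p1) + p2(1 − p2))/61].

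At 40% vs 15%: p̄ = 0.275, se0 = 0.0809, se1 = 0.0776, so (0.25 − 0.1585)/0.0776 = 1.18 and power is 88.1%. Fisher exact gives 84.3%.

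If k of 61 controls are rescued, the control rate is 0.40 − (k/61)·(r − 0.15). Here r is the event rate they would have had without rescue, and 15% is their assumed rate with it. Both are assumptions.

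| r | k | Control rate | Pooled power | Fisher power |
|---|---|---|---|---|
| 40% | 3 | 38.8% | 85.1% | 80.6% |
| 40% | 4 | 38.4% | 84.0% | 79.3% |
| 40% | 7 | 37.1% | 80.3% | 74.9% |
| 40% | 8 | 36.7% | 79.0% | 73.4% |
| 60% | 1 | 39.3% | 86.3% | 82.2% |
| 60% | 2 | 38.5% | 84.4% | 79.8% |
| 60% | 4 | 37.0% | 80.0% | 74.6% |
| 60% | 5 | 36.3% | 77.6% | 71.7% |

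Power therefore stays at 80% or more with up to 7 rescued controls (pooled) or 3 (Fisher) when r = 40%, and with about 4 (pooled) or 1 (Fisher) when r = 60%.

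**The case against.** The best defence is that the disputed clause describes rather than forbids. Section 1 says that low- and medium-risk patients do not routinely receive dietary therapy, so the sentence may only state what usual care is for the people who are eligible. Read with the Summary and section 11.4.1, a control who becomes high risk would simply fall under usual care for high risk. This reading is possible, and sensible staff may well adopt it. But section 5.1 defines the term, the definition excludes referral, and an exception would have to be inferred. What stands is that the text is ambiguous and that its literal sense is the stricter one.

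The defence is also right about scale. The MUST is not scheduled again, the trial's reassessment comes late, section 5.1 says "Patients rarely need enteral nutritional support in this prehabilitation stage", and section 11.4.1 calls the population low-risk relative to those already treated.

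A reader might infer three stronger points, and the documents do not support them.

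- *The treatment effect is biased in favour of prehabilitation.* The number of affected controls is unknown, and nothing shows that their outcomes would change the comparison.
- *The analysis plan wrongly omits this event.* Section 10 already sets intention-to-treat and a treatment-policy strategy, and it gives its intercurrent event as an example. Naming a further one can be left to an SAP.
- *The consultation count in section 8.1.3 would already show how often rescue happens.* It is a bare total. Because controls also see a dietitian during treatment, it does not isolate contacts before treatment.

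**Conclusion.** The point holds as a wording fault with a possible safety consequence. Taken literally, sections 3 and 5.1 deny a control recognised as high risk the dietitian care that the protocol itself calls standard practice, and the Summary does not go that far. The number of patients concerned is unknown and probably small. The power figures price the remedy and do not measure the fault; they rest on assumed rates for the rescued patients. This is a cheap improvement and not an error that threatens the trial's conclusion.

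**What to change.** In sections 3 and 5.1, replace the blanket exclusion with wording in line with the Summary, for example: *Controls do not receive the trial's nutritional prehabilitation. A control recognised as high MUST risk before treatment starts receives the department's usual dietitian referral and remains in the control arm for analysis.* The intention-to-treat and treatment-policy approach in section 10 already covers such patients and needs no change.

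The cost is one sentence in each of two places and a slightly smaller contrast between arms. The power lost depends on how many controls are referred and which test is used, and under Fisher's test the margin is narrow. Losing some contrast by giving controls their ordinary care is not a reason to withhold it. If the team wants to report how often this happens, dietetic contacts before treatment in controls must be counted separately from those during treatment, which is a small addition to data collection.
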